## Abstract

**Background:**

White spot lesions (WSLs) occur as a side effect in over 25 % of patients who undergo orthodontic treatment, causing aesthetic problems and a risk of deeper enamel and dentine lesions. Dutch orthodontists show substantial variation in their application of WSL preventive measures, which include little incorporation of evidence from the literature. We recently developed an evidence-based clinical practice guideline (CPG) on this topic, which was further converted into a computerized clinical decision support system (CDSS) to facilitate its incorporation into clinical practice. The present study aimed to assess the effectiveness of this CPG-based CDSS, with regard to actually preventing WSL development during orthodontic treatment with fixed appliances compared to usual preventive measures. Our study also aimed to evaluate the effects of implementing the CPG-based CDSS into routine clinical practice using a multifaceted strategy.

**Methods/design:**

We designed a hybrid effectiveness-implementation study assessing both clinical effectiveness of the CPG and its implementation into routine practice. A total of 840 patients nested in 14 orthodontic practices will be randomly assigned as clusters to the intervention or the control arm. Patients recruited by the orthodontist in the intervention group will be treated following the CPG, while the usual preventative measures will be followed in the control arm. The primary outcome measure is the proportion of patients with newly formed or enlarged WSLs after 6–9 months of treatment with fixed appliances, and at the end of treatment, using the CPG for WSL prevention compared with usual preventive measures. An additional aim is to obtain some preliminary outcomes regarding the implementation process.

**Discussion:**

This study investigates the effectiveness of a newly developed guideline to improve oral health during orthodontic treatment, while simultaneously illuminating potential difficulties in adopting a guideline in general orthodontic practice. The innovative features of this study include the risk-based CDSS that discriminates between patients’ oral health statuses with regard to preventive measure utilization in general orthodontic practices. Most studies focusing on WSL prevention apply the preventive intervention to each patient in an experimental setting, resulting in overtreatment and a disconnect from the real-world conditions in which the intervention is to be applied. Additionally, one of the overreaching goals of this initiative is to create a gold standard for WSL prevention during orthodontic treatment, against which future studies can compare new promising preventive measures and the readiness of clinicians to change and adopt new treatments. By doing so, we want to help bridge the gap between science and orthodontic clinical practice and improve the quality of oral health care.

**Trial registration:**

This trial is registered with the Dutch Trial Registry of the Dutch Cochrane Center under number NTR5012, registration date 2 March 2015.

## Background

About 53–57 % of 12-year-old Dutch juveniles undergo orthodontic treatment representing about 100,000 patients each year. Most of these patients are treated using fixed orthodontic appliances comprising metal or ceramic attachments (orthodontic brackets) that are bonded to the outer surface of the tooth and connected with wires that exert the forces required to align individual teeth. It is difficult to clean the region surrounding the bracket, making this area prone to developing dental disease or caries. Caries result when a biofilm covers an area of tooth and metabolic events within this biofilm lead to localized chemical dissolution of the tooth surface [1]. Therefore, there exists a strong relationship between caries incidence and oral hygiene among orthodontic patients compared to patients not undergoing orthodontic treatment [2].

Additionally, over 25 % of orthodontic patients show clinically visible enamel demineralization following orthodontic treatment [3]. Such enamel demineralization is considered an early stage of dental caries and is commonly referred to as a white spot lesion (WSL) due to the white appearance caused by changes in light scattering of the decalcified porous enamel. WSLs may become noticeable around the brackets within a month of bracket placement, and the opaque color seriously compromises aesthetics after debonding of orthodontic fixed appliances [4]. Although remineralization is possible, WSLs are often permanent, presenting a lifelong aesthetic problem as well as the risk of lesion progression [3, 5].

WSLs are clearly a relevant clinical problem related to treatment with fixed orthodontic appliances, and their prevention is an important concern. Numerous preventive strategies have been developed, including the maintenance of a good oral hygiene regimen involving the use of different types of mouth rinses, toothpastes, and varnishes. However, the literature describing the effectiveness of such procedures is equivocal, and largely includes study designs with high risks of bias [6] with frequent problems relating to randomization, blinding, incomplete data, and short-term follow-up [7]. Thus, orthodontists find it difficult to incorporate the existing evidence on effective preventive measures into their routine practice, and 68 % are in favor of guideline development [8].

Our research group recently developed a clinical practice guideline (CPG) on the prevention of WSLs based on the best available evidence and following a Delphi procedure to reach consensus on issues for which sound evidence is lacking [9]. However, a CPG can only impact patient outcomes if it is properly implemented into clinical practice. To facilitate the implementation of our CPG, we converted it into a computerized clinical decision support system (CDSS). A CDSS is designed to assist clinicians and health professionals with decision-making tasks, especially when the decision to initiate treatment depends on multiple patient variables, as was true for the good practice guideline (GPG) in the present study [10]. The present study aimed to assess the effectiveness of our CPG converted into a CDSS, with regard to actually preventing WSL development during orthodontic treatment with fixed appliances compared to usual preventive measures. An additional aim is to obtain preliminary outcomes on the process of CPG implementation.

## Methods/design

### Study design

We have designed a hybrid type 1 effectiveness-implementation study to primarily focus on assessing the guideline’s clinical effectiveness, while simultaneously collecting some preliminary information regarding implementation of the guideline into routine practice. The primary aim of this approach is to examine the effects of the clinical intervention (CPG) on relevant outcomes (the proportion of patients with new or enlarged WSLs), while an additional aim is to obtain preliminary outcomes on the process of CPG implementation [11].

Practitioners will be divided into two groups using cluster randomization at the level of the orthodontic practices. Patients recruited by orthodontists in the intervention group will be treated following the CPG (see intervention section), while patients recruited by orthodontists in the control arm will be treated using standard preventive measures. The proportions of patients showing newly developed or enlarged WSLs will be compared between treatment groups after 6–9 months of treatment with fixed appliances, as well as after completion of orthodontic treatment and removal of the fixed appliances.

### Primary hypothesis

The trial will evaluate the hypothesis that the preventive measures recommended by the CPG will outperform standard preventive measures with regard to the primary outcome—which is the proportion of patients with newly developed or enlarged WSLs after 6–9 months of treatment, and at the completion of treatment with fixed orthodontic appliances, with an effect size of 0.4.

### Outcome of process evaluation

The following outcomes will be analyzed to evaluate the implementation process:Professionals show a positive attitude regarding use of the CPG for WSL preventionProfessionals comply with the key recommendations for WSL prevention in the CPGPatients of the intervention clinics show a positive attitude regarding the applied preventive strategies.

### Randomization

Utilization of both the CPG and the usual preventive measures within the same practice would inevitably result in some control patients receiving some CPG-recommended care, which would dilute the effect of the intervention. To prevent such contamination of interventions between study groups, we will perform cluster randomization at the level of practices rather than individuals. Using a software program, practices will be assigned to either the *intervention arm* or the *control arm* by an independent statistician who is not familiar with the practices.

### Ethical approval

Our study protocol has been approved by the research ethics committee of the Radboud University Nijmegen Medical Center (Centrale Commissie Mensgebonden Onderzoek). The trial will be conducted following the principles of the declaration of Helsinki, and is registered with the Dutch trial registry of the Dutch Cochrane Center.

### Study population and recruitment

#### Orthodontic practices

A convenience sample of 14 orthodontists will be asked to participate in the present trial. All selected orthodontists are members of the Dutch Orthodontic Society, and work in private practices in different geographical areas of the Netherlands. In the Netherlands, a median-size practice has four to five chairs, and a mean of 40 to 60 patients receiving full fixed appliances per month. The present trial will include only practices with at least four chairs, in accordance with our aim of testing the CPG effectiveness and implementation in regular orthodontic practices. Orthodontists will be excluded if they are unwilling to take pre- and post-treatment intra-oral digital photographs. Informed consent will be obtained from all orthodontists working in each participating practice.

#### Patients

The participating orthodontists will recruit patients, following specific instructions designed to avoid selection bias. Patients in the intervention group will receive written information describing the preventive measures that will be applied. This information will be included as part of the written informed consent for orthodontic treatment that will be obtained during the treatment plan discussion prior to starting active treatment. In both groups, both patients and parents will provide written informed consent for the use of patient records and distribution of questionnaires.

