#### Sample size and power calculation

We have calculated the number of patients needed to detect a difference in the proportions of patients with newly developed or enlarged WSLs between the intervention group using the CPG and the control group using standard preventive strategies. Earlier studies show that more than 1 in 4 orthodontic patients develop at least one new WSL during the course of orthodontic treatment [3]. Assuming a power of 80 %, a significance level of 5 %, and an ICC of 0.05 to correct for clustering, we calculated that we must include a minimum of 14 orthodontic practices with 50 patients per practice to detect a medium effect size of 0.4 for reduction in newly developed WSLs. The effect size was arbitrarily chosen, as no previous data establish what would constitute a clinically relevant change. The study is powered to detect an effect of 15 % absolute reduction in prevalence of WLS, under the assumptions specified above. Assuming a drop-out rate of 20 %, we plan to recruit a total of 60 patients per participating practice, resulting in a total inclusion of 840 patients. In a regular orthodontic practice, about 40 patients receive full fixed appliances each month. To account for an overestimation of the number of patients to potentially be included in the practices, we will have a 2-month inclusion period.

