### Implementation program

The CPG will be implemented using a multifaceted intervention strategy (See Table 2.) The implementation process will be evaluated in only a limited number of practices, since this is not the primary aim of the study. First, the CPG will be disseminated by mail to the participating orthodontists in the intervention arm, together with instructions for using the CPG. One week later, the principal investigator will make an educational outreach visit to the participating practices in the intervention arm, with the goals of further explaining the recommendations in the CPG along with their rationale, and of demonstrating the use of the CDSS integrated in the EPF. Clinicians will also be provided instructions regarding the following:Evaluation of oral health in terms of the presence or absence of cavities, restorations, or WSLsEvaluation of oral hygiene level in terms of plaque index [14], using pictures of patients with varying plaque levelsHow to appropriately explain the patient’s current oral health situation, and to give appropriate advice regarding tooth-friendly nutrition and oral hygieneHow to give appropriate oral hygiene instructionHow to correctly apply fluoride varnish (Duraphat 50 mg/mL for dental use) after wire removal and tooth polishing

**Table 2 Tab2:** Implementation strategy

	Type of intervention
0	Dissemination of the CPG together with instructions for use
1 week	Educational outreach visits
5 weeks	Monitoring and feedback regarding use of the CPG through computerized patient records

The practices in the intervention group will also be given patient information folders containing the recommended oral hygiene and dietary instructions, together with the recommended letters that are to be sent to the parents and the general dentists in cases of poor oral hygiene. After 5 weeks, the number and types of preventive actions registered in the EPF will be extracted from the software and analyzed. This information will be used to give feedback to the participating practices regarding guideline adherence. For this purpose, a second visit by the principal investigator is planned, during which the practitioners will have the opportunity to discuss potential problems. This will provide insight into the problems and barriers encountered in the specific practice that may be hindering adequate guideline implementation.

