### Measurements

#### Primary outcome

The number of WSLs per patient will be determined by examination of maxillary incisors and canines, mandibular canines, and maxillary and mandibular premolars by two independent observers, who will be blinded to the patient’s intervention status. Standardized pre-treatment intra-oral photographs (T0) will be compared with intra-oral photographs taken after 6–9 months of treatment (T1), and after completion of treatment with fixed orthodontic appliances (T2). If comparison of the T0 photographs to the T1 and T2 photographs reveals an identical white spot on all three images, it will be considered a developmental white spot and will not be counted as a WSL. For each patient, the total number of new and enlarged WSLs will be registered. The proportion of patients showing new or enlarged WSLs will be determined for each group.

A pilot study using pre-and post-treatment intra-oral pictures of 150 patients from three orthodontic practices (50 patients per practice) demonstrated an inter-observer agreement of 0.6, which is considered acceptable. However, this agreement varied among the practices, mainly due to the quality of the intra-oral photographs. In the retrospective pilot study, the photographic technique was not standardized in terms of lighting and camera positioning. For the presently described prospective trial, lighting and camera positioning will be standardized, which will likely lead to better agreement. An earlier *in vitro* study measured artificially induced WSLs on extracted maxillary incisors that were photographed at different angles using standardized techniques. Their results showed non-significant interobserver differences in the surface measurements of WSLs of less than 0.1 mm [13].

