### Data collection

The data collection and timeframe are given in Table 3.

**Table 3 Tab3:** Data collection and study timeframe

Months	
1–2	14 orthodontic practices included
	Collection of baseline data (photographs of 50 treated patients and baseline questionnaire)
3	Assignment to intervention or control arm
	Information meeting
	Dissemination of CPG and educational outreach visit 1 week later*
	Professional questionnaire*
4–6	Start inclusion of patients with informed consent
10–12	Patient questionnaire
	EPF registrations
10–15	Intra-oral photographs (6–9 months into treatment)
22–30	Registration of compliance in electronic patient files*
	Intra-oral photographs
	Professional questionnaire*

* For intervention group only

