### Informed consent

Before starting treatment, all patients in both the intervention and control practices will receive a general letter containing information about the study. Patients will be informed that if they participate, they will be asked to complete a questionnaire, and information regarding oral health and oral hygiene will be extracted from their patient files. Patients at the intervention practices will be given specific information regarding the use of the CPG as part of an informed consent letter that will be signed by the patient and their parents prior to orthodontic treatment. Patients at the control practices will be receiving usual preventative care and will not be asked to give informed consent for the preventive measures used.

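### Patients are identified and recruited after allocation by orthodontists who know their practice's arm, which leaves the patient-level comparison open to recruitment bias of unknown size

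*Protocol article*

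**What the plan says.** **Order of events.** Table 3 (*Data collection*) puts "Assignment to intervention or control arm" in month 3, with an information meeting. For intervention practices only, the same month holds dissemination of the clinical practice guideline (CPG) and an outreach visit one week later. "Start inclusion of patients with informed consent" stands under months 4–6.

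**Who recruits.** *Patients* states: "The participating orthodontists will recruit patients, following specific instructions designed to avoid selection bias". The article does not give the content of the instructions.

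**What recruiters know.** According to *Implementation program*, "the CPG will be disseminated by mail to the participating orthodontists in the intervention arm". The visit that follows demonstrates the decision support system and teaches clinicians to evaluate oral health and plaque level. Control practices continue with their own measures. Patient information before entry also differs. Intervention patients sign a letter specific to the CPG, whereas *Informed consent* says: "Patients at the control practices will be receiving usual preventative care and will not be asked to give informed consent for the preventive measures used".

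**Stated protections.** *Randomization* says that "we will perform cluster randomization at the level of practices rather than individuals", with an independent statistician assigning practices. Under *Measurements*, lesions are scored by "two independent observers, who will be blinded to the patient’s intervention status". Blinding is stated for no one else.

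**Patient flow.** *Sample size and power calculation* says: "In a regular orthodontic practice, about 40 patients receive full fixed appliances each month". *Orthodontic practices* gives a mean of 40 to 60. The target is 60 patients per practice over a 2-month inclusion period.

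**The concern.** In a cluster-randomised trial, allocating practices at random makes the practices comparable apart from chance. The patients within them are comparable only if the arm has no influence on who is identified, judged eligible, approached and persuaded to consent. Here all four steps come after allocation and lie with clinicians who know it.

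The knowledge that differs between arms also bears on prognosis. Shortly before inclusion, only the intervention orthodontists have been taught to grade the features that predict white spot lesions (WSLs). If this, or enthusiasm for the CPG, or arm-specific consent, changes the risk profile of those enrolled, the arms differ before any preventive measure is applied. Blinded photograph readers would record that difference accurately, and the multilevel logistic model would attribute it to the intervention. More patients or more practices would not remove it.

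**Working it through.** **Step 1: sequence.** Allocation is in month 3, CPG mailing and training follow in month 3, and inclusion is in months 4–6. The order is stated in Table 3 and does not depend on detail that the article leaves out.

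**Step 2: what each protection covers.**
- The independent statistician protects the assignment of practices, which is complete before any patient is recruited.
- Blinded observers protect the scoring of lesions, which happens after the patients have been enrolled.
- The recruiter instructions are the only protection aimed at patient entry. They act on people who know the arm, so they can limit selection but cannot conceal allocation.

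**Step 3: room for selection.** Flow = monthly number × 2 months.
- 40 × 2 = 80, so 60 places are 60/80 = 75% of the flow.
- 60 × 2 = 120, so 60 places are 60/120 = 50% of the flow.

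These counts cover all patients receiving full fixed appliances. They come before the 12–18 age limit, the dentition requirement, the exclusions and consent. If 75% of 80 are eligible and consent, 0.75 × 80 = 60 and no surplus remains.

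**Step 4: the benchmark.** The stated 15-point reduction, from about 25%, gives 25% v 10%. With a two-sided 5% level (assumed, as sidedness is not stated) and 80% power, this needs 100 patients per arm. The design effect is 1 + (50 − 1) × 0.05 = 3.45. Then 2 × 100 × 3.45 / 50 = 13.8, which reproduces the stated 14 practices. The sample size is not in dispute; 15 points serves only as the yardstick.

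**Step 5: illustration (inputs assumed).** Let one arm leave out a fraction q of its candidates, whose risk is r, while the other arm recruits without selection. Overall risk is 25%.

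Rate among those enrolled = (0.25 − q × r) / (1 − q)

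| q | r | Rate enrolled | Spurious difference |
|---|---|---|---|
| 0.25 | 0.40 | (0.25 − 0.10)/0.75 = 20.0% | 5.0 points |
| 0.25 | 0.30 | (0.25 − 0.075)/0.75 = 23.3% | 1.7 points |
| 0.10 | 0.40 | (0.25 − 0.04)/0.90 = 23.3% | 1.7 points |
| 0.10 | 0.30 | (0.25 − 0.03)/0.90 = 24.4% | 0.6 points |
| 0 | any | 25.0% | 0 |

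**Step 6: a second set of assumptions.** Let half the pool be high risk (35% v 15%, or 40% v 10%), with high-risk patients left out twice as often. From a pool of 80, 20 are left out (13.3 high, 6.7 low), so 26.7 high and 33.3 low remain. The rate is (26.7 × 0.35 + 33.3 × 0.15)/60 = 23.9%, or (26.7 × 0.40 + 33.3 × 0.10)/60 = 23.3%. The shift is 1.1–1.7 points. From a pool of 120, 20 high and 40 low remain. The rate is 21.7% or 20.0%, a shift of 3.3–5.0 points.

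**The case against.** The strongest reply has four parts.

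1. **Safeguards may exist.** The article says that instructions against selection bias are given and, being condensed, need not spell them out. They may require consecutive enrolment, and eligibility is open to all patients who meet the criteria. This stands against a reading that some will find tempting, namely that orthodontists hand-pick 60 from 80 or more candidates. The article does not say so. Free choice is an inference, and the 80–120 is not a count of eligible patients. *Sample size and power calculation* itself sets the 2-month period as a guard against overestimating how many can be included. The reply does not meet the narrower point. Even under consecutive enrolment, recruiters who know the arm apply the criteria that need judgement and conduct arm-specific consent.

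2. **The hygiene exclusion is narrow.** It covers only patients whose physical or mental problems rule out adequate oral hygiene. That is correct, and it cannot be read as a general route for leaving out ordinary poor brushers. It still calls for a judgement by the recruiter on something close to lesion risk.

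3. **Imbalance can be examined.** Oral health and hygiene at the start are registered in control practices too, covariates are entered in the model, and each practice's past WSL incidence is measured. This helps to detect measured imbalance. However, the covariates enter one by one, and unblinded practices record the patients' initial status. The past incidence comes from patients already treated, so it describes the practice and not the trial's recruits.

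4. **The bias figures rest on assumed inputs.** This is conceded in full. They show scale and are not an estimate.

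**Conclusion.** The point holds as a weakness in the stated order of events: recruitment follows allocation and is done by people who know it, and no stated protection conceals the arm at patient level. The direction and size of any bias are unknown. Under the first illustration, with a quarter of one arm's candidates omitted, the spurious difference is 1.7–5 points against the 15-point target. It shrinks towards zero if the real surplus is small. More extreme assumptions give larger shifts, but nothing in the article points to them.

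A reader might infer that 25–50% of candidates will be left out at the orthodontist's discretion, or that a 5-point bias follows from the protocol's own figures. Neither is supported. The percentages describe all fixed-appliance patients before eligibility and consent, and the risk among those omitted is assumed. The change is worth making because it is cheap, and because selection that has already occurred cannot be reliably undone in the analysis.

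**What to change.** Change the order in Table 3:

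- **Before allocation is opened (months 1–2).** Each practice lists from its electronic patient file (EPF) the patients aged 12–18 scheduled for full fixed appliances in the inclusion months. It applies to that list every eligibility criterion that can be judged at that stage, including the judgement on physical or mental incapability of proper oral hygiene.
- **After allocation.** The practice approaches patients strictly in list order, adding any scheduled later consecutively by planned bonding date, until 60 have consented.
- **Log.** The reason for each non-enrolment is recorded, and numbers and reasons are compared by arm.

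The cost is one EPF export and one screening log per practice, with no extra patients. It assumes that planned bonding dates can be extracted from the EPF, which the article does not confirm. Some listed patients will reschedule.

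The change reduces the risk but does not remove it. Patients scheduled later are still identified after allocation. Consent still follows allocation and differs by arm, and refusal of prescribed products cannot be judged beforehand. These should be reported as residual risks.
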